# Methods to ensure the safety of study participants:

Risk and benefits of use of rifampin and of high dose rifampin are detailed in the consent form and reviewed in section “Background” of the protocol (pages 6-11).

Rifampin is a safe drug that has been used by millions of people to treat TB disease for about 45 years. Minor side effects of rifampin include headache, tiredness, weakness, gastro-intolerance, diarrhea, itchiness, rash or loss of appetite. These usually resolve spontaneously, and it is not necessary to stop the treatment. More serious reactions, such as hepatitis, are more rare. Usually hepatitis resolves once treatment is stopped.

Rifampin can also cause tears, sweat, spit, bowel movements and urine to turn orange during treatment. Contact lenses might stay stained with this orange color.

Rifampin can also affect other medications, see more details in “Concomitant treatment” at page 16.

Side effects are expected to be similar in nature to standard dose, and frequency has been similar when used in previous studies, as reviewed in “Background” (pages 6-11).

This trial will have several mechanisms to ensure the safety of study participants. During treatment phase participants will be followed closely with regular visits at which questions are asked about occurrence of new symptoms as well as laboratory monitoring as described above. All new symptoms will be recorded and managed with appropriate follow-up by the treating team. Participants will also be encouraged to call or visit the study centre if they experience any new symptoms. If at any time during treatment (up to 30 days after end of treatment) an adverse event is suspected by study staff, or treating team, this will be investigated, managed and reported following strict protocols that vary according to the type of adverse event. (Note: for possible adverse events occurring after end of treatment, investigations needed and reporting is decided on a case by case basis by site investigator and coordinating center). Adverse events of grade 3 or 4; and rash of any grade, that are considered possibly or probably drug-related will require study medication **permanent discontinuation**. Providers may, on an individualized basis, decide to continue or restart the study drug if the AE was a mild rash (Grade 1-2) or an alternate explanation was found. For example, another drug or food was ingested that could have caused the rash. In these circumstances close follow-up (i.e. daily or every other day) is required and if the rash worsens, management should be re-evaluated.

For other suspected Grade 1-2 drug-related adverse events, the treating team will decide if study medication should be discontinued on a case by case base. If treatment can be continued, the symptoms will be noted in follow-up forms, and the patient followed as judged necessary by the treating team. If the study drug is stopped by the treating team for more than 48 hours because of a suspected adverse event, including a new potential drug interaction, the site investigator must enter an initial AE report on the web-site, within 24 hours of deciding to stop the study drug, or becoming aware of the event. Note: this initial report must be completed for all events of Grade 3 or higher even if they do not require drug discontinuation. This initial report triggers an automatic notification to the coordinating centre, who will review the report within 24 hours. The PI will be notified immediately of all adverse events that are Grade 3, 4 or death. Staff at the coordination centre will contact the site PI to verify the situation, remind them of the procedures for diagnosis and management of a suspected outcome. These staff will continue to monitor the AE – as it is investigated and managed. The DSMB (see below) will be notified immediately of all Grade 3-4 AE that the PI believes were not anticipated, and were possibly related to the study regimens, and any deaths that the PI believes could possibly be related to the study regimen. Unexpected serious adverse events related to study drug, will also be reported to local IRB and to Health Canada.

When the investigation has been finalized (and/or the event has resolved), the site PI will complete the AE final report. This will be reviewed by coordinating center staff (unblinded), who will verify if the report is complete, and check that no information about the regimen used is included in the report. Once this is completed the PI [name] will review the blinded report. This is to check again for any event that was serious and unanticipated (which are to be reviewed immediately by the DSMB). This will also serve as a final check to ensure that the report is complete and coherent enough that the adjudication panel can render judgments.

Then the full blinded report will be made available to the 3-member panel for adverse events. This panel will function as in our prior 4R vs 9H trial. All three panel members will make independent judgements about the AE – severity, type, and likely attribution to study regimen (unlikely related, possibly related, or probably related). If judgments are discordant we will take the majority opinion (two out of three). If all three opinions are discordant, then the panel will be asked to re-review. If the panel raises concerns about a particular AE report, these concerns will be communicated to the PI, and to the chair of the DSMB at the same time.

These same procedures will apply if virtual follow-up is done. In case participants need to be seen for investigations and follow-up related to a possible adverse event an in-person visit will be scheduled as soon as possible.

Participants who permanently stop treatment with high dose rifampin will discuss alternative options with their treating medical team. During initial site training, medical teams at participating sites will be informed of the different options for participants. Depending on the reasons why high dose rifampin was stopped the alternatives could be: taking rifampin, but at the standard dose, taking an alternative LTBI treatment approved by the national TB programme of the country (such as INH) or having close follow up with periodic symptoms screen and chest-x ray for early detection of active TB. The choice of the alternative would be individualized and decided by the primary health care provider and the participant.

All participants who permanently stop the study drug (either in high dose or in standard dose arm) will be followed after the stop of study treatment as per “Follow-up post treatment” procedures of all other participants who completed the study treatment, until 26 months from randomization.

At the end of the post-treatment follow-up, all participants will be provided with instructions about symptoms of active TB, and how to seek medical care if symptoms of active TB arise. They will also be given a card with information on the trial and contact information for the treating and research teams. The card will specify that the efficacy of the experimental treatment is not yet proven and therefore the risk of developing active TB could be higher than in people treated with the current standard regimen.

Data Safety and Monitoring Board (DSMB)

The DSMB will be responsible to review two planned interim safety analyses, also will review on an ad-hoc and immediate basis any Grade 3-4 adverse events that are unexpected, as well as any deaths that occur during treatment phase (regardless of the judgement about possible role of study drugs in the death). Ad-hoc reviews of unexpected serious adverse events and deaths will be done whenever needed.

Note that a few serious adverse events (but not deaths) can be *expected* as these occurred in our prior trials with 4R_10._ These will not be brought to the attention of the DSMB when they occur, but will be included in all safety analyses, and they are also mentioned in the consent, and will be explained to the potential participants’ during the consent process.

The two planned interim safety analyses, and procedures for unblinding are explained in more detail in Statistical analysis section (page 21). The DSMB will review the results of these two planned analyses and make recommendations regarding continuing or stopping enrolment to study arms, or the overall study. All DSMB recommendations, and the results of the planned interim analyses will be sent to the research ethics committees at all participating sites, and the trial steering committee.

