# Rationale:

We propose a phase 2b trial initially to assess acceptability, tolerability and safety – through the combined outcome of completion, plus a careful assessment of safety through detailed independent review of all Grade 3 or worse adverse events. This trial will have several mechanisms to ensure safety of study participants, including review within 24 hours by the coordinating centre of all adverse events associated with suspension of study drug, subsequent review by an independent panel of all potentially serious drug related adverse events, and periodic as well as ad hoc review of safety data by an independent data safety and monitoring board (DSMB). If this trial demonstrates that higher doses of rifampin are as well tolerated and safe as standard doses of rifampin, and when given for two months have better completion, this will justify a full-scale phase 3 future trial to assess efficacy of these regimens. If the highest dose (30mg/kg/day) is equally well tolerated as the 20mg/kg/day dose, then we will select the highest dose for the phase 3 trial. On the other hand, if the 30mg/kg/day dose is less well tolerated or associated with a higher rate of serious adverse events then we will use the 20mg/kg/day dose in phase 3.

We propose an open label trial for duration – because the difference in duration is the expected key determinant of treatment completion and the short duration of only two months is the major advantage for patients. Since there is a possibility of worse tolerability and safety with higher doses, the difference in duration is necessary to offset any potential disadvantages of the short higher dose regimen. We have used an open label design successfully in previous trials; to overcome potential bias in ascertainment of outcomes we will utilize blinded independent review panels for the outcomes of adverse events and active TB – as we have done in past studies (Diallo et al. 2018; Menzies D et al. 2008; Menzies et al. 2018). We will blind the two higher doses, as we expect that patients and health care providers may be more likely to report side effects with the higher doses, and the duration is the same.

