# Outcomes

## Primary outcomes

The study has two primary outcomes: regimen completion and safety

Regimen completion: we have selected regimen completion as one of the two primary outcomes because we consider this to represent a summary measure of tolerability – i.e. the combined impact of patient decision to stop due to symptoms, such as stomach upset, anorexia, or fatigue, and health care provider decision to stop based on objectively measured events such as rash, or liver or hematological toxicity. This outcome has the additional advantages of being easy to define and measure, and does not require the added judgment of investigators, or an outside panel. Treatment completion is also readily comparable to completion measured in other studies.

This outcome will be based on the number of pills dispensed and pill counts during treatment phase follow-up visits. For the 2-month high-dose rifampin regimens, treatment phase medical follow-up visits by patients will be made two weeks after the start of therapy, at 4 weeks, and at end of therapy, and for 4R_10_ after 1 and 2 months and at end of therapy (total 3 follow-up medical visits for each regimen). Completion will be defined as taking 80% of doses within 120% of allowed time (48 doses within 72 days for the two-month regimens, and 96 doses within 144 days for the 4-month regimen).

Safety: Grade 3 to 5 adverse events (and Grade 1-2 rash) which result in permanent discontinuation of the study drug, and that are considered probably or possibly related to the study drug by the majority of a three-member independent and blinded Adverse Events panel. This panel (see below for details on panel) will review all events when the study investigator / primary health care provider stopped the study drug permanently because of their concerns of a potential drug-related adverse event. The panel will review these incidents blinded to rifampin dose, and independently from each other. Grading will be standardized using criteria established by the American Thoracic Society for hepato-toxicity (Saukkonen et al. 2006) and the National Cancer Institute for all other adverse events (National Cancer Institute Terminology Criteria for Adverse Events v4.0, at: <https://evs.nci.nih.gov/ftp1/CTCAE/CTCAE_4.03/Archive/CTCAE_4.0_2009-05-29_QuickReference_8.5x11.pdf>

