| **Grade 3-4, n (%)** | 31 (0.9) | 74 (2.3) | -1.4 (-2.0, -0.8) |
| **Grade 5 (Death), n (%)** | 0 | 1 (0.03) | -0.03 (-0.1, 0.03) |
| **Adverse Event Type (in adults)**  **(Judged Related to Therapy)** |  |  |  |
| **Grade 3-4 Hepatotoxicity, n (%)** | 11 (0.3) | 65 (2.0) | -1.7 (-2.2, -1.2) |
| **Grade 1-4 Rash, n (%)** | 25 (0.8) | 13 (0.4) | 0.4 (-0.01, 0.7) |
| **Grade 3-4 Hematologic, n (%)** | 6 (0.2) | 0 | 0.2 (0.04, 0.3) |
| **Grade 3-5 Other, n (%)** | 8 (0.2) | 8 (0.2) | 0 (-0.3, 0.2) |
| **Results in children (0-17)** |  |  |  |
| **Total Number treated** | N=422 | N=407 |  |
| **Serious Adverse Event, n** | 1 (death) | 1 (pregnancy) | 0 |
| **Serious adverse events attributed to treatment** | 0 | 0 | 0 |
| **Did not have any follow-up visits (N, %)** | 26 (6.2) | 25 (6.1) |  |
| **Seen at least once in follow-up (N, %)** | 396 (93.8) | 382 (93.9) |  |
| **Average (STD) % of visits during follow-up when any minor symptom was reported** | 8.1 (20.3) | 8.5 (18.9) | -0.3% (-3.3, 2.7) |
| **Average (STD) % of visits during follow-up when a minor symptom that may have been related to the study drugs was reported** | 4.4 (14.5) | 4.2 (11.1) | 0.3% (-1.7, 2.4) |

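### For Grade 1-2 rash the protocol both requires and waives a permanent stop, so a provider who knows the regimen decides whether the rash can count as a primary safety event

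*Protocol*

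**What the plan says.** All section names refer to the Protocol.

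- *Methods to ensure the safety of study participants*, default: "Adverse events of grade 3 or 4; and rash of any grade, that are considered possibly or probably drug-related will require study medication" to be discontinued permanently.
- Same section, next sentence: "Providers may, on an individualized basis, decide to continue or restart the study drug if the AE was a mild rash (Grade 1-2"), or if another explanation was found. Close follow-up is then required, with re-evaluation if the rash worsens. Nothing says when the provider should stop and when continue.
- Same section, general description of rifampin, on a list of minor side effects that includes rash: "These usually resolve spontaneously, and it is not necessary to stop the treatment".
- *Primary outcomes*, safety: "Grade 3 to 5 adverse events (and Grade 1-2 rash) which result in permanent discontinuation of the study drug", provided a majority of the blinded panel judges the event possibly or probably related. The panel's stated remit there is events for which the drug was stopped permanently.
- *Rationale*: "We propose an open label trial for duration". *Design* confirms that only 20 versus 30 mg/kg is blinded.
- Reporting, in the safety section: the web AE report is triggered by a stop of more than 48 hours for a suspected adverse event, or by any event of Grade 3 or higher. Separately, all new symptoms are to be recorded, and suspected adverse events investigated, managed and reported.

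**The concern.** For Grade 1-2 rash the permissive sentence cancels the mandatory one. The exception covers every mild rash, so the any-grade wording is left applying only to Grade 3-4 rash, which the same sentence already covers as a Grade 3-4 event. Restarting also does not fit a discontinuation that is meant to be permanent.

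This would be a drafting matter if the stop were only a management step. Here it is part of the endpoint definition. Two participants with the same mild, drug-related rash can differ in the primary safety outcome solely because one provider stopped and the other did not. The provider knows whether the course is the short high-dose one or the standard one. If the habit of stopping differs between these groups, the risk difference against 4R10 shifts, and it can shift either way: more caution at high dose adds events there, while more willingness to see a short course through removes them.

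The protocol's safeguard against open-label bias is blinded adjudication. That protects the judgement of relatedness among rashes that were stopped. It cannot restore a rash that was continued.

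**Working it through.** **Step 1. Follow one Grade 1-2 rash, suspected to be drug-related, through the text.**

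| Provider's decision | Web AE report | Can be a primary safety event |
| --- | --- | --- |
| Permanent stop | Yes | Yes, if the panel majority judges it possibly or probably related |
| Held more than 48 hours, then restarted | Yes | No, the stop was not permanent |
| Held 48 hours or less, or continued | Not explicitly required; recorded as a symptom | No; no explicit route to the panel |

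**Step 2. How much of the outcome passes through this gate.** Appendix 2, Table S7, 4R adults (3280 treated), events judged related to therapy: 31 Grade 3-4 stops and no Grade 5; 11 hepatotoxicity, 6 hematologic and 8 other at Grade 3 or above; 25 in the row "Grade 1-4 Rash, n". Assuming the event types do not overlap:

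- Grade 3-4 rash = 31 − (11 + 6 + 8) = 6
- Grade 1-2 rash = 25 − 6 = 19, or 19/3280 = 0.58%
- Events under the *Primary outcomes* definition = 31 + 19 = 50, or 50/3280 = 1.52%, against 31/3280 = 0.95% without mild rash
- Share that is mild rash = 19/50 = 38%

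At 412 per arm and the 4R rate this is about 412 × 31/3280 = 3.9 events without mild rash and 412 × 50/3280 = 6.3 with it.

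**Step 3. Reproduce the plan's safety sample size.** Table 3: margin 4%, 4 contacts per household, ICC 0.05, so design effect 1 + 3 × 0.05 = 1.15. With 80% power and one-sided alpha 0.05,

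n = (1.645 + 0.842)² × (p0·q0 + p1·q1) / (0.04 − (p1 − p0))², with q = 1 − p, multiplied by 1.15.

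- 1% vs 2%: 203 × 1.15 → 234, as in Table 3
- 2% vs 3%: 335 × 1.15 → 386, as in Table 3

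One-sided 0.025 gives 297 and 489, so Table 3 rests on one-sided 5%.

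**Step 4. Let stopping of mild rash depend on the arm.** Power = Φ((0.04 − (p1 − p0))/SE − 1.645), SE = √((p0·q0 + p1·q1) × 1.15/412). Here 412 is the analysable number per arm from *Sample size considerations*. The mild-rash rate is assumed equal, 0.58%, in every arm, so any change comes from stopping alone.

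Grade 3-5 rates 1% (4R10) vs 2% (high dose):

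| Mild rashes stopped | p0 | p1 | Power |
| --- | --- | --- | --- |
| All, both arms | 1.58% | 2.58% | 88% |
| High-dose arm only | 1.00% | 2.58% | 79% |
| 4R10 arm only | 1.58% | 2.00% | 98% |

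First row: SE = √((0.01555 + 0.02513) × 1.15/412) = 0.01066; 0.03/0.01066 − 1.645 = 1.17; Φ = 0.88.

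With Grade 3-5 rates of 2% vs 3% the three figures are 75%, 63% and 90%.

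**The case against.** The best defence is that the safety section states a default followed by an exception, with close follow-up attached, and that this is a normal way to write a management rule. That is a fair reading of the intent. It does not answer the point, because the exception takes in every Grade 1-2 rash and has no criterion, so for mild rash nothing mandatory remains.

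It can also be said that provider discretion runs through this trial. Stopping for other Grade 1-2 events is decided case by case; open-label duration is acknowledged and justified; and completion is deliberately a summary of patient and provider decisions to stop. This stands, and for that reason the effect on completion is not pressed here. The difference for safety is that mild rash is the only Grade 1-2 event named in the primary safety outcome.

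Some stronger readings are tempting but not supported:

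- A reader might count three competing stop rules. The remark that stopping is not necessary is background on rifampin in general, qualified by usually. It sits badly with the mandatory sentence but gives no instruction.
- A reader might infer that a continued rash goes unreported. The protocol records all new symptoms, speaks generally of reporting suspected adverse events, and triggers a web report once the drug is held for more than 48 hours. The sentence "If treatment can be continued, the symptoms will be noted in follow-up forms" belongs to a paragraph on Grade 1-2 events other than rash, so it does not settle the matter. What is missing is an explicit web-report and panel route for a rash continued or held for 48 hours or less.
- A reader might take the protocol to predict different stopping by dose. The *Rationale* expects more reporting of side effects at higher doses, as the reason for blinding 20 against 30 mg/kg. It does not mention stopping.
- A reader might compare power with every mild rash stopped (88%) and none counted (95% at 1% vs 2%). That contrast measures whether mild rash belongs in the endpoint, which is a different question.

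Finally, a sensitivity analysis is usually left to the SAP. That is so, but data capture is not: an analysis plan cannot recover relatedness judgements that were never collected.

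**Conclusion.** The point holds as a design weakness of moderate weight. The mandatory and permissive sentences conflict for Grade 1-2 rash, and the unresolved choice, made by someone who knows high dose from standard dose, decides whether the rash can enter a primary outcome.

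On the earlier 4R data, 38% of events under the *Primary outcomes* definition pass through this gate. At the protocol's planning rates, stopping that depends wholly on the arm moves non-inferiority power from 88% to 79% or 98% (1% vs 2%), or from 75% to 63% or 90% (2% vs 3%). These are all-or-nothing extremes; partial differences would move it less.

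The figures rest on non-overlapping event types in Table S7, an equal mild-rash rate of 0.58% in all arms (the documents give none for high dose), design effect 1.15 and one-sided 5%. They also use the *Primary outcomes* definition. The *Objectives* section names only Grade 3 to 5 events; if that governed, mild rash would leave the primary safety outcome. Nothing in the documents shows that stopping will in fact differ by arm, only that the design would not detect or correct it.

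**What to change.** 1. In *Methods to ensure the safety of study participants*, reconcile the mandatory and permissive sentences, and the general remark that precedes them, so that one stop rule for rash with its exception applies identically in all arms. What the rule should be is for the clinicians.
2. In the reporting paragraph of that section, require an AE report, forwarded to the blinded panel, for every rash suspected to be drug-related, including those continued or restarted.
3. Add a sensitivity analysis of the safety outcome that counts every Grade 1-2 rash the panel judges possibly or probably related, whether or not the drug was stopped, and report use of the exception by arm.

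The cost is protocol wording, one extra analysis, and a few more short reports and panel reviews. At the earlier 4R rate of stopped mild rash this concerns about 0.6% of participants, or 1359 × 19/3280 ≈ 8 people. It could be more, since that rate leaves out rashes that were continued and high dose may cause more rash.

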- Active TB – the incidence of active TB (microbiologically confirmed and all forms) in the 26 months post-randomization per 100 person-years of follow-up will be compared between all three arms.

All analyses will include adjustment for clustering by household. In stratified analysis, results will be presented by indication for LTBI treatment. Sensitivity analyses will be conducted where by analysis are stratified by study centre and by country.

Interim analyses

To optimize protection of safety of study participants, we plan at least two interim analyses of study regimen completion and of Grade 3-5 adverse events. The first analysis will be conducted after the first 150 participants randomized (i.e. approximately 50 in each arm) have completed therapy. This means we will assess outcomes that have occurred in each of these individuals up to 146 days post-randomization. The second interim analysis will be conducted 146 days after randomization of the 450^th^ Participant – i.e. after approximately 150 participants should have completed therapy in all 3 arms. However, as described below, the 2^nd^ analysis may be performed sooner if there are concerns about excess toxicity with either high-dose arm.

Our goal is to identify as early as possible if the high dose rifampin regimens are associated with a clinically important increased rate Grade 3-5 AE, or intolerance – defined as failure to complete therapy. The study bio-statistician will conduct both interim analyses in a blinded fashion. Given that there are two planned interim analyses, the p value -adapted for multiplicity of testing- that will be used to consider significant the difference between proportions is of p<0.022 (Pocock’s method).The Data Safety and Monitoring Board (DSMB – see below for more details) will also consider results while remaining blinded to the identity of the regimens. For each interim analysis, if any of the regimens meets criteria for a clinically important difference in adverse events or completion, then we will unblind in step-wise fashion. If unblinding is deemed necessary, the person in charge of code breaking will be the principal investigator ([name]) and the study coordinator ([name]). Same procedures will be followed if DSMB asks for unblinding in specific cases for serious and unexpected adverse events.

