# Study committees

Scientific Advisory Committee (SAC)

The responsibilities of the SAC are to provide advice and recommendations regarding scientific aspects of the studies, particularly study design, interventions and outcomes as well as the statistical analysis plan. We have already formed a SAC for all projects within the CIHR Foundation grant.

Members of the SAC are: [name], Chief Scientist at the World Health Organization in Geneva; [name], director of Denver Public Health and long-standing member of TB Trials Consortium; [name], director of Science, TB division, Centre for Disease Control, Atlanta, Georgia and scientific director of TB Trials Consortium; [name], professor of University of Melbourne, Australia – considered the global authority on pediatric tuberculosis; [name], epidemiologist and modeler at McGill International TB center.

Data Safety and Monitoring Board (DSMB)

The DSMB will be responsible to review the two planned interim analyses, as well as any unexpected Grade 4 adverse events, or deaths that could be related to study regimens. All DSMB recommendations, and the results of the planned interim analyses will be sent to the research ethics committees at all participating sites, and the trial steering committee.

The current DSMB (originally constituted for the 4R vs 9H trial) includes: [name] [name], chair, formerly director of science at Centre for Disease Control (USA), [name], director of the TB centre of Southeast USA (Gainesville, Florida), and [name], Professor of Medicine in Infectious Diseases at the University of Colorado Denver School of Medicine, Denver, USA.

Trial steering committee

The trial steering committee will review progress of the ongoing trial, including enrolment and randomization, pragmatic problems such as difficulties with enrolment or withdrawal of consent, as well as need for study amendments. The trial steering committee will also review recommendations of the SAC and the DSMB. The trial steering committee will be responsible for the final decision regarding stopping enrolment to any study arm, or the study. If such a decision is taken, the research ethics committees at all participating sites will be notified.

This committee will be comprised of the principal investigator ([name]), the Foundation project manager ([name] ), the 2R^2^ trial coordinator ([name]), and the trial biostatistician ([name]) as well as the qualified investigators from each of the six sites.

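### Interim results on both primary outcomes go, with no stated masking or confidentiality limit, to a steering committee that includes the principal investigator, the code-holding coordinator and all six site investigators

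*Protocol*

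**What the plan says.** Under Statistical analysis (Interim analyses), the protocol states that "we plan at least two interim analyses of study regimen completion and of Grade 3-5 adverse events". The suggested guidance to the DSMB is framed as differences from the standard arm.

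The DSMB part of the safety section says that "the results of the planned interim analyses will be sent to the research ethics committees at all participating sites, and the trial steering committee". Study committees repeats the rule: "All DSMB recommendations, and the results of the planned interim analyses will be sent to the research ethics committees at all participating sites", and again adds the steering committee. Ethical considerations likewise sends all interim results to the IRB. In each place results travel in addition to the DSMB's recommendations.

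On membership of the steering committee: "This committee will be comprised of the principal investigator", the project manager, the trial coordinator and the trial biostatistician, "as well as the qualified investigators from each of the six sites". On its powers: "The trial steering committee will be responsible for the final decision regarding stopping enrolment to any study arm, or the study".

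On masking, the biostatistician runs both interim analyses blinded and the DSMB starts without knowing regimen identity. If unblinding is judged necessary, "the person in charge of code breaking will be the principal investigator", together with the study coordinator, and identity is then disclosed to the DSMB in steps. The section on drug accountability says that the central study coordinator already knows the code for the high-dose arms.

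On the outcomes, the adverse events panel reviews events "when the study investigator / primary health care provider stopped the study drug permanently because of their concerns" about a drug-related event. Regimen completion is described as reflecting both patient and provider decisions to stop.

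**The concern.** Comparative interim results are normally kept from those who recruit, treat and make judgements that enter the endpoint. Here a written rule sends them to the lead investigator at every site. It is not a detail left open for a later document: a DSMB charter that withheld the results would contradict the protocol.

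The protocol recognises the hazard elsewhere. It avoids unblinding the DSMB without need because this could bias the board's decisions. It blinds the two high doses because patients and providers may report more side effects if they know the dose. Yet it sets no limit for people closer to the data than the DSMB.

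At stake are the later judgements made at sites: whether an event is drug-related, whether to stop the drug, how firmly to encourage completion, and whom to approach for enrolment. Participants and sites know whether treatment lasts two or four months, so a belief about which duration is doing worse could act differently on the two.

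**Working it through.** The question is who sees what, so most of the check sets the sections side by side.

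**1. Content and recipients.** The interim analyses cover completion and Grade 3-5 adverse events (Statistical analysis). The results go to the steering committee and ethics committees (safety section, Study committees, Ethical considerations). None of these places says whether what is sent is pooled, coded or identified, or that recipients must keep it confidential.

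**2. How far the stated masking reaches.** It covers the biostatistician's analysis and the DSMB's first review. Three features weaken it for the steering committee:
- The coordinator, a member, holds the dose code for drug supply. The principal investigator, also a member, breaks the code with the coordinator when needed.
- Duration is open label, so only 20 versus 30 mg/kg is hidden at sites.
- The step-wise procedure creates cases in which identity is known and the trial goes on. If the standard arm looks worse, that fact is revealed to the DSMB and all three arms continue. If only the 30 mg/kg arm has the excess, enrolment to that arm stops. The steering committee takes that final decision, so it must know which arm it is stopping while the others continue.

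**3. Route to the outcomes.** The safety outcome needs permanent discontinuation by the investigator or provider, and as defined under Primary outcomes it includes Grade 1-2 rash. The safety section requires discontinuation for Grade 3-4 events and any rash considered possibly or probably drug-related. That consideration is a site judgement, and for mild rash or an alternative explanation providers may continue or restart. The blinded panel protects grading and attribution, but an event without permanent discontinuation is not a primary event. Completion depends partly on the treating team's encouragement (During treatment).

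**4. Participants potentially exposed.** Planned total 1359; interim triggers at 150 and 450 randomized.
- After the 150th: 1359 − 150 = 1209; 1209/1359 = 89%.
- After the 450th: 1359 − 450 = 909; 909/1359 = 67%.

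Both are upper bounds. Nothing pauses recruitment while outcomes mature to 146 days, so some of these participants will have been treated before results circulate. The protocol gives no accrual rate from which to narrow the figure.

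**5. Sensitivity of the safety comparison.** Analysable number per arm 412; expected control rate 1% to 2% (Sample size considerations).
- Expected events: 412 × 0.01 = 4.1 to 412 × 0.02 = 8.2.
- Two altered decisions in one arm: 2/412 = 0.5 percentage points.
- Three: 3/412 = 0.7 percentage points.
- Share of the 4-point margin: 0.485/4 = 12% to 0.728/4 = 18%.

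Two or three is an assumed number, chosen to show scale. The protocol gives no basis for estimating how many decisions would change, or how far completion would move.

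**The case against.** The strongest reply is that the text does not say the committee sees results by identified arm. The analysis and the DSMB review are masked, code breaking is conditional and shared with the coordinator, and it serves disclosure to the DSMB. This stands. A reader might infer that every site investigator learns the comparison with arms named, or that the principal investigator is unblinded as a matter of course. The documents support neither.

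A reader might also infer that the standard arm could be picked out of any coded table, because its completion rule is 96 doses in 144 days rather than 48 in 72. That is not shown: a table of percentages completing and percentages with events need not display doses or days, and outcomes are taken to 146 days in all arms.

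Discretion is also narrower than it may look. Stopping is required for Grade 3-4 events considered drug-related, scheduled blood tests make some events objective, completion rests on pill counts, and adherence support follows normal clinic procedures. Every Grade 3 or higher event must be reported initially even if the drug continues, and the Rationale section promises independent review of all such events. These points reduce the room for bias. They do not remove the site's judgement of relatedness, its latitude over mild rash, or the need for discontinuation before an event counts.

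The principal investigator's blinded check of adverse event reports is partly protected, since unblinded staff first remove regimen information and the panel adjudicates.

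**Conclusion.** The point holds as a question of information flow. Results of both interim analyses go, without a stated limit, to a committee containing the people whose sites generate both primary outcomes. Coded-arm results are the most the text establishes, but the coding is a weak barrier given who holds or can break the code and what the committee must know in order to act.

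The size is a potential, not a demonstrated, bias: at most 67% of participants are randomized after the second trigger, and an assumed two or three altered stopping decisions in one arm would use 12% to 18% of the non-inferiority margin. No movement in completion can be quantified from the documents. This should be fixed, and before the first interim analysis, because disclosure cannot be undone. It does not by itself invalidate the design.

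**What to change.** Amend the DSMB text in the safety section, Ethical considerations and Study committees so that the steering committee and ethics committees receive only the DSMB's recommendation. Results should be released only if the DSMB recommends stopping an arm or the trial; the steering committee then still has what it needs for its final decision.

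Amend Interim analyses so that the closed report, and any code break for the DSMB, are handled by a statistician independent of both trial conduct and the steering committee, not by the principal investigator, the coordinator or site staff. The coordinator can keep the code for drug supply, provided coded interim results do not reach the coordinator.

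The cost is a wording amendment, matching text in any DSMB charter, and the naming of an independent statistician. Investigators and ethics committees would not see interim data while the trial continues. The DSMB's safety oversight is unchanged.
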